## Materials and methods

### Study design

The PAINLESS study, funded by Horizon Europe (call HORIZON-HLTH-2021-DISEASE-04; Project ID: 101047367), is an international multicenter, randomized, placebo-controlled, triple-blind, three-armed clinical trial to test the efficacy of 15 sessions of home-based tES in patients with chronic cancer-related pain. We will explore the effects of anodal tDCS of the left M1 and 10 Hz tACS over the DLPFC on clinical pain, quality of life, cognitive and emotional functioning, fatigue, sleep quality, as well as psychophysical and neurophysiological markers of central pain processing using QST and EEG respectively. Measurement visits will take place at baseline (T0), post-tES intervention (T1), and three months (T2) following the intervention. At the last visit, six months (T3) following the intervention, only the NRS of intensity, unpleasantness and interference of cancer pain with daily life, as well as the NRS of fatigue and sleep quality, will be assessed.

A randomization list is created for an independent researcher for all the clinical sites involved. The study flowchart is described below and summarized in Table 1.

**Table 1 Tab1:** Study protocol

		Base line	15-days tES intervention		Follow up		
Study activities	Screening Visit 1	Visit 2 (T0)	Visit 3 (Session 1)	Sessions 2–15	Visit 4 (T1)	3-months follow up Visit 5 (T2)	6-months follow up Visit 6 (T3)
Location of meeting	Home or Clinic	Clinic	Clinic	Home	Clinic	Clinic	Home
Screening	✔						
Informed consent and anamnesis	✔						
Baseline questionnaires		✔					
Clinical Interview and History	✔	✔			✔		
NRS pain assessment		Pain intensity rated daily on NRS including 15 days baseline recording				✔	✔
tES training for home stimulation			✔				
Battery of questionnaires		✔			✔	✔	✔
QST-EEG		✔			✔	✔	
Medication diary			✔	✔	✔	✔	
Side/adverse effects questionnaire			✔	✔	✔		
Home-based feasibility questionnaire					✔		
Blinding and satisfactory questions					✔	✔	✔

*tES* transcranial electrical stimulation, *NRS* numerical rating scale, *QST* quantitative sensory testing, *EEG* electroencephalography.

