#### Visit 6. Six-month follow-up (Telephone or online; T3)

Six months after the tES intervention, investigators will call the patients via telephone or online to measure the core clinical outcomes on an NRS scale with a one-week recall period. No QST or EEG will be performed. Caregivers will fill in their respective set of questionnaires. The socio-economic questionnaire and a satisfaction survey will also be administered to both patients and relatives/caregivers.

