### Specific aims and hypotheses

This multicenter study will address many aspects of cancer-related persistent pain including its potential treatment with repeated tES and assessment of the effectiveness of the therapy using self-reported assessment of different symptoms of the disease, psychophysical testing using QST and neurophysiological testing using EEG. The aims and hypotheses of the study are as follows:Aim 1: To determine the therapeutic effects of 15-day home-based anodal tDCS and tACS interventions (compared to sham stimulation) on pain intensity (primary outcome), other dimensions of pain (pain unpleasantness, catastrophizing, interference), quality of life, cancer-associated symptoms (fatigue, depression, anxiety, sleep fragmentation, cognitive impairment), and global functioning among patients with cancer-related persistent pain. We hypothesize that compared to sham, tDCS and tACS will reduce clinical pain and associated symptoms as well as improve quality of life and global functioning. We expect that anodal tDCS might have a stronger effect on pain intensity, while tACS can have a stronger effect of decreasing stress, emotional processing of pain and improving quality of life. We will also test the feasibility of the home-administered tES (analyzing dropout rates, satisfaction scores, adverse and side-effects…). The potential long-term benefits of the interventions will also be addressed at three and six months post-treatment follow-ups.Aim 2: To identify psychophysical and neurophysiological predictors and mediators of tES-induced analgesia in patients with cancer pain. We hypothesize that the improvement in clinical pain will be mediated by intervention-induced adaptive changes in (i) nociceptive and pain modulatory system using QST indices and through contact heat-evoked potentials (CHEPs) using concurrent heat painful stimuli and EEG, as well as (ii) in oscillatory activity measured by resting state EEG.Aim 3: To identify responders to the tES interventions based on clinically relevant reduction in pain intensity (≥ 30%) and to characterize them according to central pain biomarkers using QST, EEG measures and/or sociodemographic, climical and disease related data. We hypothesize that indices of pain modulation and perception will be sensitive to predict treatment outcomes.

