### Secondary outcomes

#### Self-reported questionnaires

Patients will fill in a battery of scales and questionnaires at T0, T1 and T2, using the PAINLESS platform. At T3, only some of the scales will be delivered telephonically or online.

Pain and its dimensionsThe NRS for pain unpleasantness [0: not unpleasant at all; 10: maximum unpleasantness of pain] will be reported daily 15 days pre-, during, and post-treatment, similar to NRS for pain intensity, and assesses the impact of the intervention on the affective-motivational dimension of pain. NRS will also be assessed at T0, T1, T2, and T3 visits with a one-week recall window. This score has been shown to exhibit good sensitivity as well as discriminant and convergent validity and sensitivity to change [55].The NRS for the interference of cancer-related pain in daily life during the last day [0: no interference at all; 10: maximum interference] will be reported daily 15 days pre-, during, and post-treatment, to address the extent to which cancer pain hinders the individual’s engagement with their daily activities.The 9-item Brief Pain Inventory (BPI) assesses pain holistically, including the history, location, severity, and impact. The Pain severity (Items 3 to 6) and the Interference components (Item 9) of the BPI will be used as outcome variables [56]. Higher scores indicate higher severity.The 13-item Pain Catastrophizing Scale (PCS) tests the level of pain catastrophizing in patients, defined as exaggerated negative cognitive-affective response to actual or anticipated pain experiences [57, 58]. Higher scores reflect higher levels of catastrophic thinking. The overall score will be calculated (range 0–52), with a total score of >30 indicating a clinically significant level of pain catastrophizing. High levels of pain catastrophizing in cancer patients with chronic pain have been associated with reduced quality of life and higher levels of pain, fatigue, and sleep impairment [59].Quality of lifeThe total score of the 36-Item Short Form Survey (SF-36) (Ware, 2000), a commonly used and validated questionnaire to assess the quality of life in different populations of cancer patients and across countries [60–63], will be used to determine the quality of life of participants (range 0–100). Higher scores indicate higher quality of life.The European Quality of Life 5 Dimensions 3 Level Version (EQ-5D-3 L) instrument [64, 65], a valid and reliable questionnaire in both European and non-European cancer patients [66–68], will also be used to measure health-related quality of life.Composite scores of these two questionnaires will be also investigated.FatigueThe 21-item Modified Fatigue Impact Scale* (*MFIS) [69, 70] will be administered to assess the level of fatigue, a debilitating consequence of cancer, affecting over half of cancer patients [71, 72]. The scale accounts for the physical, emotional, and social components of fatigue and the overall score ranges from 0 to 84, with higher scores representing higher levels of fatigue.Sleep qualitySleep fragmentation is one of the most distressing symptoms impeding the quality of life of cancer patients throughout all stages of the disease and all phases of treatment, with a prevalence of 60.7% of sleep disturbance [73]. The 12-item Sleep Scale from the Medical Outcomes Study (MOS) scale [74], a frequently used subjective assessment of sleep disturbance in patients with malignant or chronic illnesses [75–79], will be used to assess sleep quality of patients. The aggregated MOS score (range 11–71) will be calculated, with higher scores representing greater sleep dysfunction.Performance statusThe 6-point scale Eastern Cooperative Oncology Group (ECOG) scale [80] (0: fully functional and asymptomatic, 1: symptomatic, fully ambulatory, 2: symptomatic, in bed or chair < 50% of the day, 3: symptomatic, in bed or chair >50% of the day, 4: bed- or chair-ridden, 5: dead) will be administered to assess how the patient’s disease is progressing and evaluate how the illness affects their abilities of daily living, including self-care.Psychological impairmentThe 9-item Patient Health Questionnaire (PHQ-9) [81, 82], a self-administered instrument for screening, monitoring, and assessing the severity of depression, will be used to assess the depression level of the participants. Higher scores are associated with higher levels of severity.The 7-item Generalized Anxiety Disorder (GAD-7) scale [83] will be implemented to assess the level of anxiety in patients, with higher scores indicating higher levels of anxiety.Cognitive functioningCognitive complaints are one of the most common consequences of cancer and its treatment, and have a negative impact on the well-being of patients. The 20-item *ONCOFOG (OFQ) questionnaire* will be used to assess the cognitive complaints (including different domains such as attention, memory, etc.).Subjective improvement and satisfactionThe participants will fill in an ad-hoc questionnaire. The instrument will aggregate all the physical and emotional functioning, side effects etc. into an overall measure of their perception of the advantages and disadvantages of the treatment received.Medication diaryThe participants will record their daily use of medication, including type and dose, in a medication diary throughout the study.Socioeconomic statusA socio-economic variables questionnaire will be administered to explore the financial costs of cancer (direct and indirect, medical and non-medical costs) for patients in home care. Its analysis will enable assessment of the socioeconomic cost/benefit associated with the tES treatment.

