### Statistical analysis plan

The statistical plan was accepted by the ethical committees of the involved centers. To ensure that the treatment groups (tDCS, tACS, sham) were comparable, we will perform a one-way analysis of variance (ANOVA) for age, gender, clinical outcomes and a chi-squared analysis for the demographic variables, medication pattern, and the rest of categorical variables.

 Aim 1 and 2: We will implement an intention-to-treat analysis approach, including all randomized participants who received at least 10 consecutive stimulations [101, 102]. Missing data will be imputed following the method that allowed us to obtain the best adjustment. We will address our primary and secondary hypotheses using two complementary statistical approaches (Classical Frequentist and Bayesian statistics) to enhance the robustness of our findings (similar to Samartin-Veiga et al., 2022), as well as time series analysis. We will calculate mixed model ANOVAs for each outcome (scores of self-report questionnaires for both patients and care providers, as detailed in Sect. 4.2; QST and EEG measures) with the intervention group (tDCS, tACS, sham) as a between-subject factor and time (T0, T1, T2, T3) as a within-subject factor. Age, sex, and cancer characteristics (i.e., type extension, evolution, previous treatments) will be included as covariate variables in the statistical analysis. In the presence of statistically significant main effects and group*time interaction effects, Bonferroni-Holm corrected post hoc analyses will be conducted for multiple comparisons. The effect size will be computed as eta squared η2 and interpreted based on Cohen’s benchmark categorization (small, η2 = 0.01; medium, η2 = 0.06 and large, η2 = 0.14) [103]. The normality of residuals will be tested using Shapiro Wilk’s test and normality plots. The homoscedasticity assumption for mixed model ANOVA will be tested with the Levene’s test and the sphericity will be tested using the Mauchly’s test for repeated factors. In case of sphericity deviation, Greenhouse-Geisser corrections will be used.

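### The QST and EEG models include a six-month visit at which neither is measured, the patient scales collected at that visit are described inconsistently, and the analysis stated for Aim 2 does not test its mediation hypothesis

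*Protocol article*

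**What the plan says.** The section Statistical analysis plan assigns one method to Aims 1 and 2 together: a mixed ANOVA for each outcome. The outcomes listed are the patient and care-provider questionnaires and the "QST and EEG measures) with the intervention group (tDCS, tACS, sham) as a between-subject factor and time (T0, T1, T2, T3". The same section adds a Bayesian counterpart and a time series analysis, without saying what either would estimate.

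On the six-month visit (T3) the article says:

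- Visit 6: "No QST or EEG will be performed". Patients give core outcomes on an NRS and complete a socio-economic questionnaire and a satisfaction survey; caregivers complete their own set.
- Study design, text: "only the NRS of intensity, unpleasantness and interference of cancer pain with daily life", together with NRS ratings of fatigue and sleep quality.
- Study design, Table 1: QST-EEG is ticked at T0, T1 and T2 only, but the row "Battery of questionnaires" is ticked at T3 as well.
- Self-reported questionnaires: "Patients will fill in a battery of scales and questionnaires at T0, T1 and T2, using the PAINLESS platform", and then "At T3, only some of the scales will be delivered telephonically or online". The scales are not named.

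Specific aims and hypotheses defines Aim 2 as finding predictors and mediators of the analgesic effect, and states: "We hypothesize that the improvement in clinical pain will be mediated by intervention-induced adaptive changes in" QST indices, contact heat-evoked potentials and resting EEG.

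**The concern.** The stated model does not match the visit schedule for the mechanistic outcomes, and the stated test does not match the mechanistic hypothesis. The first means that an analyst following the text cannot run the QST and EEG models. For the patient questionnaires, the analyst cannot tell which have a T3 value. The second matters more for interpretation. The introduction makes the mechanisms of pain relief the study's secondary objective, and the abstract expects arm differences in mechanistic measures to yield candidate biomarkers. If the only analysis is whether a marker differs by arm, a marker that moves with treatment but has nothing to do with pain relief could be reported as a mechanism.

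**Working it through.** **1. Time factor against schedule (QST and EEG).** Planned levels: T0, T1, T2, T3, so 4. Collected: T0, T1, T2, so 3. Missing by design: 1/4 = 25% of cells, for 450 of 450 patients. Patients with all four values: 0. The plan names Mauchly's test and Greenhouse-Geisser corrections, which points to a classical repeated-measures ANOVA, and that has no complete case to use. A likelihood-based mixed model would not help, because a T3 mean or arm-by-T3 contrast cannot be estimated from no observations. Limiting the factor to three visits changes the interaction degrees of freedom from (3−1)(4−1) = 6 to (3−1)(3−1) = 4.

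**2. Does dropping T3 for these outcomes disturb the sample size?** Inputs from Sample size calculation: f = 0.095, alpha 0.05, power 0.90, N = 291, recruitment 450 for about 30% loss. The article gives neither the number of visits m, the correlation rho, nor the effect tested, so these are assumed. For the group-by-time interaction with k = 3 arms and sphericity (epsilon = 1):

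lambda = f²·N·m/(1−rho), df1 = (k−1)(m−1), df2 = (N−k)(m−1).

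- The stated figure: m = 3, rho = 0.5 gives N = 288 (lambda = 0.009025 × 288 × 3/0.5 = 15.6), within about 1% of 291. But m = 4, rho = 0.4 gives 294, so 291 does not reveal how many visits were assumed.
- Three visits, rho = 0.5: power is 90.5% at N = 291 and 92.8% at N = 315 (450 × 0.70).
- Four visits, rho = 0.5: N = 246, with power 95.0% at N = 291.
- Range for three visits: rho 0.4 needs 345, rho 0.5 needs 288, rho 0.6 needs 231. At rho = 0.5 with epsilon = 0.75, 354 are needed.

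At rho = 0.5 with sphericity, three visits are consistent with the stated N. At rho = 0.4, or with epsilon = 0.75, power for these secondary outcomes would fall below 90% with 315 patients.

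**3. Patient scales at T3.** Side by side: NRS items only (Study design text); the whole battery (Table 1); an unnamed subset (Self-reported questionnaires); NRS outcomes plus socio-economic and satisfaction questionnaires (Visit 6). The analysis section applies four time levels to all of them.

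**4. Do separate ANOVAs test mediation?** This is an illustration with assumed inputs; the article gives no path values. Patients: 315 split 2:2:1 = 126/126/63. Let A = 1 for either active arm and 0 for sham. Marker change M = 0.5A + e1; pain change Y = (0.5 − 0.5b)A + bM + e2, with e1 and e2 standard normal. The total arm effect on Y is 0.5 for every b, and b is the marker-to-pain path. Each of 2,000 simulated trials had a three-arm ANOVA of each change score (equivalent to the interaction over two visits) and a joint-significance mediation test with the active arms pooled.

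| b | ANOVA, marker | ANOVA, pain | Both ANOVAs | Mediation test |
|---|---|---|---|---|
| 0 | 89% | 91% | 81% | 5% |
| 0.3 | 89% | 86% | 78% | 94% |
| 0.6 | 90% | 77% | 72% | 95% |

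The pair of ANOVAs is significant about as often with no mediation as with it. The slight fall with b arises because the within-arm variance of pain change is 1 + b². Only the test that links M to Y separates the cases.

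**The case against.** The strongest reply is that this is a condensed article and that the details of a mediation model belong in a full analysis plan that is not shown. That stands for the details: the type of interval, the sensitivity analysis and the choice of pain summary are preferences. It does not remove the point, because the article explicitly assigns the per-outcome ANOVAs to Aim 2, and nothing links the Bayesian or time series analyses to mediation.

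A second reply is that listing T3 in one pooled time factor is a drafting slip, since the schedule makes clear that no QST or EEG is planned then. That is fair as to its origin and explains why it is easily repaired.

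Three stronger readings might be inferred, and the article does not support them:

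- *That Aim 2 as a whole cannot be answered.* Its text does not depend on six-month QST or EEG, and the predictor part is partly covered by the model trees under Aim 3, which use biomarkers to profile responders.
- *That questionnaires are not collected at T3.* Caregiver sets, NRS items, socio-economic and satisfaction questionnaires and some patient scales are. The fault is inconsistency about which patient scales. These mostly serve Aim 1.
- *That the T3 QST and EEG values would be invented by imputation.* The plan says missing data will be imputed; it does not say that visits never scheduled will be.

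**Conclusion.** The point holds in three parts. The four-level time model cannot be fitted for QST and EEG, where T3 is empty for every patient; this rests on the article's text and Table 1 and needs no assumption. The article contradicts itself on which patient scales exist at T3. The mediation hypothesis of Aim 2 is not tested by the analysis stated for it; the 81% against 5% contrast shows why this matters, but its size depends on the assumed effects and sample. The primary pain NRS is collected at T3 and is not affected. The correction should be made before analysis, because the mechanistic conclusions depend on it.

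**What to change.** 1. In Statistical analysis plan, give the time levels per outcome: T0, T1 and T2 for QST and EEG; T3 only for outcomes collected then.
2. Name the patient scales collected at T3 once, and bring Table 1, the Study design text, Visit 6, Self-reported questionnaires and Statistical analysis plan into line with that list.
3. For the mediation part of Aim 2, name a mediation analysis: each active arm against sham, the T1 QST or EEG marker as mediator, and pain over the 15 daily ratings after treatment as outcome, adjusted for baseline marker and baseline pain. Report the indirect effect with an interval and state the assumption of no unmeasured confounding between marker and pain.
4. State that the Aim 3 trees serve the predictor part of Aim 2, if that is intended.

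Cost: changes of wording and some analysis work, with no new data, because the T1 markers and the post-treatment daily ratings are already planned. The downside is that the indirect effect is not protected by randomization and rests on the stated assumption. Its power cannot be given from the article, which has no inputs for either path.

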## Assessments and measures

### Primary outcome

The primary outcome will be self-reported cancer pain intensity, assessed by using the 11-point NRS [0: no pain due to cancer; 10: intolerable pain due to cancer] [52, 53]. The cancer pain intensity will be reported daily on the PAINLESS platform for 45 days (15 days pre-treatment, 15 days during, and 15 days post-treatment, recorded about the same time of the day). In addition, it will be reported at T0, T1, T2 and T3 visits with a recall period of 1 week. The reproducibility and cross-cultural validity of the NRS have been shown in chronic cancer-related pain, making it a reliable measure for pain assessment as a clinical outcome in many studies [54].

We will follow an intention-to-treat approach with missing data being imputed following the method that allows us to obtain the best adjustment.

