### Sample size calculation

To calculate the sample size, we considered the data of a recent meta-analysis of 13 studies with data originating from 398 participants with chronic pain. Active tDCS has been reported to have a superior effect than sham with a medium-large size effect (standardized mean difference= −0.76 +/– CI 95% = −1.24) [100]. However, the effect size of tDCS varied considerably between studies, for which reason we decided to achieve small effect sizes to ensure the robustness of our results. Thus, we used G*Power software (Version 3.1.9.7) to calculate the sample size sufficient to reach a small effect size (f = 0.095) with mixed model analysis of variances (ANOVA), setting alpha at 0.05 and power (1-β) at 0.9. The sample was estimated as 291 participants. Thus, we will recruit 450 participants to compensate for eventual dropouts or attrition during the treatment or at the follow-ups (approximately 30%).

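### The one specified efficacy model treats baseline as an outcome, puts active-versus-sham behind omnibus tests including a diluted group main effect, and fixes no primary contrast for the daily pain ratings

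*Protocol article*

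**What the plan says.** - **Primary outcome.** Pain intensity on the 0 to 10 NRS is collected in two forms: "The cancer pain intensity will be reported daily on the PAINLESS platform for 45 days" (15 days before, 15 during and 15 after treatment), and "In addition, it will be reported at T0, T1, T2 and T3 visits with a recall period of 1 week".
- **Hypotheses.** The section on specific aims and hypotheses states that each active stimulation will reduce pain relative to sham. These are two pairwise contrasts.
- **Model.** The section Statistical analysis plan specifies a mixed ANOVA with group (tDCS, tACS, sham) between subjects and "time (T0, T1, T2, T3) as a within-subject factor". The covariates are age, sex and cancer characteristics; baseline pain is not among them. The outcomes listed in brackets are the Sect. 4.2 questionnaire scores (apparently the secondary outcomes), QST and EEG.
- **Pairwise tests.** "In the presence of statistically significant main effects and group*time interaction effects, Bonferroni-Holm corrected post hoc analyses will be conducted for multiple comparisons".
- **Other analyses.** The same section addresses the primary and secondary hypotheses "using two complementary statistical approaches (Classical Frequentist and Bayesian statistics) to enhance the robustness of our findings", and adds a time series analysis without stating its data, summary or contrast.
- **Planning.** The sample size rests on f = 0.095 in a mixed ANOVA, "setting alpha at 0.05 and power (1-β) at 0.9". "The sample was estimated as 291 participants", and 450 are recruited to cover roughly 30% loss.

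**The concern.** Three features of the specified analysis do not serve the stated hypotheses.

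1. **The gate.** Read word for word, active versus sham is tested only if the main effects and the interaction are all significant. The group main effect averages T0, when nobody has been treated, with visits up to six months later. It is not the treatment effect, and it is small whenever the benefit fades. The aims call long-term benefit only potential, so fading is realistic.
2. **Baseline.** With T0 as an outcome level and no baseline covariate, the treatment contrast is in effect a difference in change scores. Conditioning on baseline is more precise.
3. **The primary comparison is not fixed.** The daily series stands first in the definition of the primary outcome but has no stated summary, time window or contrast. Three analytic approaches address the same hypothesis and none is said to decide.

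At stake is whether a real short-term effect can be declared, and whether the deciding version of the outcome is chosen before or after results are known.

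**Working it through.** **Step 1: the plan's own figure.** For a within-between interaction, λ = f²·N·m/(1−ρ), with df (k−1)(m−1) and (N−k)(m−1). The article gives no correlation; ρ = 0.5 is assumed. With k = 3 groups and m = 3 measurements, 90% power needs N = 287 (288 as a multiple of 3), and 291 gives 90.5%. With the four visits of the analysis section, N = 244 suffices and 291 gives 95%. The stated 291 is therefore broadly reproduced (the match is not unique) and is not the problem.

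**Step 2: analysed sample.** 450 × 0.7 = 315, which at 2:2:1 is 126/126/63.

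**Step 3: difference implied by f = 0.095.** Assume SD 1 and the same effect d in both active arms. Under 2:2:1 the between-arm factor is 0.8 × 0.2 = 0.16, so f = d·√(0.16·V), where V is the variance over T0 to T3 of the effect profile.

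- Sustained (0, 1, 1, 1) or T1 only (0, 1, 0, 0): V = 0.1875, so d = 0.095/√0.03 = 0.548.
- Waning (0, 1, 0.5, 0.25): V = 0.1367, so d = 0.095/√0.0219 = 0.642.
- With three equal groups the factor is 2/9, and a sustained or T1-only profile gives d = 0.465. This is used below as a smaller effect.

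**Step 4: power of the two omnibus tests at N = 315.** The mean of four visits has variance (1 + 3 × 0.5)/4 = 0.625. For the group test, λ = 315 × 0.16 × (d × mean profile)²/0.625 on 2 and 312 df.

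- Sustained: mean profile 0.75, λ = 13.65, power 0.92.
- Waning: mean profile 0.4375, λ = 6.37, power 0.61.
- T1 only: mean profile 0.25, λ = 1.52, power 0.18.

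For the interaction, λ = 0.095² × 315 × 4/0.5 = 22.74 on 6 and 936 df, power about 0.96 for every profile. Under compound symmetry the two numerators are independent, so the joint power is close to the product: 0.89, 0.59 and 0.17. Simulation gives the values in the table. The time main effect adds no further loss as long as pain changes over time in all arms; with an assumed common fall of 0.3 SD after T0 it was always significant.

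**Step 5: direct contrast.** For tDCS versus sham at T1, adjusted for T0, the residual variance is 1 − 0.5² = 0.75. The standard error is √(0.75 × (1/126 + 1/63)) = 0.134. Holm is applied over the two active-sham contrasts.

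| Difference at T1 | Profile | Group and interaction both significant | Interaction alone | Direct, Holm |
|---|---|---|---|---|
| 0.548 SD | sustained | 0.88 | 0.96 | 0.98 |
| 0.642 SD | waning | 0.58 | 0.96 | 0.99 |
| 0.548 SD | T1 only | 0.17 | 0.96 | 0.98 |
| 0.465 SD | sustained | 0.71 | 0.88 | 0.91 |
| 0.465 SD | waning | 0.27 | 0.74 | 0.91 |
| 0.465 SD | T1 only | 0.11 | 0.88 | 0.91 |

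The loss comes from requiring the group main effect, not from the interaction test.

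**Step 6: baseline adjustment.** Change-score variance is 2(1−ρ); baseline-adjusted variance is 1−ρ². At ρ = 0.5 these are 1.00 and 0.75, a 25% reduction. At ρ = 0.7 they are 0.60 and 0.51, a 15% reduction.

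**The case against.** **The daily ratings may be analysed.** A reader might infer that they are left out altogether. The article does not support that: time series analysis is named for the primary hypotheses and is a natural place for a 45-day diary. The one-week-recall NRS at T0 to T3 also belongs to the primary outcome, so a T0 to T3 model does analyse part of it. What stands is that the daily series has no specified summary or contrast and no analysis is named as decisive. A separate plan may settle this, but the article does fix the model and the gate.

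**The gate sentence has a milder reading.** ANOVA reports often use such wording to mean that each significant effect gets its own post hoc tests. A significant interaction would then be enough, and the loss is small at f = 0.095. It is therefore wrong to say without qualification that most of the power is lost: that needs the literal reading together with an effect that is confined to T1 or, at the smaller difference, waning. What stands is that two defensible readings give 0.17 or about 0.96 for a T1-only effect.

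**Baseline as an outcome level is valid.** In a randomised trial it gives an unbiased comparison. Adjustment is a gain in precision whose size depends on an unstated correlation.

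**Two further inferences are not supported.** One could compute an inflated family-wise error (7 to 14%) by counting success on any of two to four versions of the outcome. The article never says that any one version suffices and presents the approaches as complementary. One could also argue that the T1 recall week mostly covers treatment days, but the article gives no date or window for Visit 4.

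**Conclusion.** The concern holds in a limited form. The specified model places the trial's actual question behind omnibus tests, forgoes baseline adjustment, and leaves the daily ratings without a primary contrast.

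Read literally, the gate lowers power from 0.98–0.99 to about 0.88, 0.58 or 0.17 for a sustained, waning or T1-only effect at f = 0.095. At 0.465 SD it falls from 0.91 to 0.71, 0.27 or 0.11. Under the interaction-only reading, the interaction test has about 0.96 at f = 0.095 and 0.74 to 0.88 at 0.465 SD.

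These figures assume 315 analysed, four visits, correlation 0.5, compound symmetry and equal effects in both active arms. None of these except the number of visits is fixed by the article; the 315 follows from its approximate 30% loss. The stated sample size is not in error.

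**What to change.** Before unblinding:

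1. Name two primary contrasts, tDCS versus sham and tACS versus sham, on one version of pain NRS. One suitable choice is the mean of the 15 post-treatment daily ratings, adjusted for the 15-day pre-treatment diary mean.
2. Test both directly with Holm and no omnibus gate.
3. For the other outcomes, use the T0 value as a covariate instead of a level of the outcome.
4. Label the T0 to T3 ANOVA, the Bayesian analysis and the time series analysis as supportive.

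**Cost.** No new data and no extra patients, since both diary periods are already collected. The during-treatment ratings and the mixed ANOVA become secondary. The sample-size statement, now tied to the mixed ANOVA, should be re-expressed for the two contrasts with its assumed SD and correlation.
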